### 4.4. Procedures for the Patients in the Control Group

Check whether the patient meets the inclusion criteria for the experiment.Check whether the patient meets the exclusion criteria.Discuss the purpose and procedures of the experiment with the patient’s parents/guardians and obtain their informed consent for the child’s participation in the experiment. This includes consent for the processing of personal data and the use of biological material samples for scientific purposes, as well as consent for participation in surveys and follow-up on the effectiveness of therapy.Collect blood parameters indicating inflammation (leukocytosis, CRP, procalcitonin) at the “0” point (“BEFORE intervention”), between signing the consent form and the fifth day of the child’s life.Ensure that biological material samples (feces, urine and blood samples) are collected before (point “0”) FMT, as described in the section below, or collect samples before the sixth day of the child’s life.For the control group, the matching time point for administering gut microbiota doses and counting “post” days is assumed to be the sixth day of the child’s life.From day 6 (the matching time point), any adverse events or deviations from the norm will be recorded, such as deterioration in general condition, appearance of symptoms of infection or increase in inflammation indicators.Blood inflammation parameters (leukocytosis, C-reactive protein (CRP), procalcitonin) will be collected during the “post-matching time point” period at least once within 72 h of day 6, or more frequently if the patient’s clinical condition requires it, as assessed by the attending physician.

The following will also be recorded in both study groups:-The number of days spent in hospital;-Percentage increase in body weight (birth weight vs. weight at discharge);-The number of days of antibiotic therapy received during hospitalization (monitoring until discharge from the hospital conducting the experiment).

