#### 2.3.6. Temporary Exclusion Criteria

Criteria for temporary postponement of microbiota administration (study group) and postponement of the matching time point for administration of intestinal microbiota doses (control group) if, prior to FMT or on day 6 of life, at least one of the following occurs as identical for microbiota administration and up to day 14 of life:Oral feeding intolerance: (assessed by the qualifying physician on the day of the planned FMT) if any of the following are present:
-Painful abdominal distension and/or visible intestinal loops.-Blood in the stool.-Increased gastric residuals:
Two consecutive episodes exceeding >50% of the volume of the previous portion.Two or more consecutive episodes of retention/bilious or duodenal residuals/emesis—when these episodes are not related to anxiety, delayed stool passage, the possibility of swallowing blood during delivery or from damaged nipples, incorrect positioning of the gastric catheter, bleeding from the nasal cavity.Increased gastric residual volume is not defined as a volume of up to 2 mL if the newborn receives a feeding portion of 1–2 mL.

Suspected NEC based on Bell’s criteria.Antibiotic therapy during planned FMT administration.Clinical/laboratory/radiological signs of infection—if at least one of the following clinical signs and/or more than one laboratory and/or radiological sign is present:
-Clinical symptoms of infection:
Hemodynamic instability: hypotension, tachycardia, peripheral circulation disorders (according to age norms), thermoregulation disorders, and fever > 38 °C, hypothermia < 36 °C.Apathy, lethargy, and convulsions.Apnea and deterioration of respiratory efficiency.
-Laboratory symptoms of infection:
Elevated inflammation parameters: leukocyte count< 5 and >30 thousand/μL up to 48 h and <5 and >20 thousand/μL > 48 h; left shift in neutrophil differential I:T > 0.2 for >34 h and >0.16 for <34 h.Platelet count < 50 K, coagulopathy.CRP > 0.05 mg/L (normal range < 0.05–1 mg/L); PCT (>72 h) > 0.5–1 ng/mL (normal range 0.5–1 ng/mL).Positive cultures of normally sterile body fluids.
-Radiological signs of infection, including systemic infection, e.g.,
Gallbladder bed edema.Unexplained pulmonary hypertension suddenly detected by echocardiography.

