## 4. Detailed Procedure

### 4.1. Transplant Recipients Procedures

FMT will be administered to patients in the study group who meet the inclusion criteria and do not meet the exclusion criteria, in the form of a deep rectal infusion, in a volume of 5 mL, twice at 6 h intervals, between 3 and 6 days after birth and/or up to 14 days in patients who experience temporary contraindications to the use of FMT or in patients who will be transferred to our center for treatment from an external facility.

In the first phase of the experiment, 10 patients from the study group born between 28 0/7 and 36 6/7 will undergo the procedure. All adverse effects of the therapy will be monitored and documented on an ongoing basis. If no serious adverse events (SAEs) occur, we will include another 10 patients born between 24 0/7 and 27 6/7 in the study (phase two of the experiment).

A serious adverse event (SAE) is defined as any medical event that, at any dose, meets at least one of the following criteria:Leads to death.Is life-threatening to the participant.Requires hospitalization or prolongs hospitalization.Leads to permanent or significant impairment of function or disability.A detailed description of the monitored parameters is provided below.

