### 4.2. Protocol for Administering Fecal Microbiota Preparation

Check whether the patient is eligible for FMT therapy according to the inclusion criteria.Assessing possible contraindications to FMT therapy (according to the exclusion criteria).Discuss the therapy with the patient’s parents/guardians and obtain their consent for the child to participate in the experiment. Also obtain consent for the processing of personal data and the use of biological material samples for scientific purposes, as well as for participation in surveys and follow-up on the therapy’s effectiveness.Collection of blood inflammation parameters (leukocyte count, CRP and procalcitonin) at the “point 0” stage, i.e., before the administration of microbiota.Ensure that biological material samples are collected before (point “0”) FMT (feces, urine and blood samples), as described in the section below. Alternatively, collect samples before administering FMT.Familiarize yourself with the characteristics of producing donor intestinal microbiota preparations in the form of a suspension (MBiotix^®^ HBI; Warsaw, Poland) and with the procedure for administering the therapy to patients.Verify the presence of temporary contraindications to FMT administration.Obtain the FMT preparations from the storage location.Thaw the suspension in accordance with the characteristics of the FMT suspension production service and/or the manufacturer’s instructions. The suspension does not require special thawing conditions; allow the syringe to thaw in an uncovered container at an ambient temperature of 22–25 °C for approximately 2–2.5 h.Administer two doses of intestinal microbiota (FMT1 and FMT2).

Due to the high safety profile of this form of FMT administration, patients will receive the preparation via deep rectal infusion using a soft Foley catheter.

The catheter will be connected to a syringe containing the suspension, and its lumen will be filled with the suspension to minimize the risk of oxygen entering the intestinal lumen.

The Foley catheter will then be inserted into the rectum to a depth of approximately 10–15 cm. After placement, 5 mL of the preparation (from a syringe containing 8 mL of the suspension) will be slowly administered directly into the catheter. Ultrasound guidance will be used to confirm the correct position of the Foley catheter and ensure the preparation is administered to the correct location—the cecum area.

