### 4.3. Monitoring the Transplant Recipients After the Procedure

Based on experience with FMT, the highest risk of developing sepsis, a rare but dangerous complication, occurs within the first six hours after the preparation is administered. Therefore, after the procedure, the patient will be continuously monitored.

The following will be assessed for the next 72 h after FMT administration:The number of episodes of oral feeding intolerance, diarrhea and the presence of blood, mucus or pus in the stool.The appearance of symptoms of infection or significant changes in vital signs (ECG, heart function and saturation—continuous measurement; blood pressure—4 times a day; temperature).The number of cases of NEC developed.Observation of other symptoms, such as convulsions, inconsolable crying and anxiety.The number of positive blood cultures and the percentage of antibiotic therapy use.Number of serious adverse events (SAEs), e.g., death, serious threat to health and/or life, and/or deterioration of health.

Blood inflammation parameters (leukocyte count, CRP and procalcitonin) will be collected before administration of the preparation (FMT1) and no later than 6–12 h after administration of FMT2, then every 12–24 h up to 72 h after FMT, depending on the patient’s condition.

A blood culture will be taken in the event of a significant increase in inflammatory parameters.

If any of the above-described criteria for temporary postponement of microbiota administration occur between FMT1 and FMT2 but resolve within 6 h (reassessment of the child’s condition after a minimum of 6 h) and do not recur within the next 6 h, the second dose of microbiota (FMT2) may be administered.

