## 5. Expected Results

### 5.1. Primary Outcome

The primary outcome is safety, assessed through adverse event reporting and comparison with the control group.

Examination of the safety profile includes analysis of all adverse events, including any deviations from the norm: deterioration in general condition, appearance of symptoms of infection, and increase in inflammation indicators.

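### The control baseline inflammation panel is capped at day 5 of life and the study-group panel only by FMT1, so postponed controls get a stale baseline and late-transferred controls cannot comply

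*Protocol article*

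**What the plan says.** **Control baseline.** Section 4.4 places the point-0 panel "between signing the consent form and the fifth day of the child"'s life. The same section puts the control matching point, from which adverse events are recorded, at day 6.

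**Study-group baseline.** Section 4.2 asks for the panel "at the “point 0” stage, i.e., before the administration of microbiota". Section 4.3 says the markers "will be collected before administration of the preparation (FMT1) and no later than 6–12 h after administration of FMT2". Both give a latest time only. Section 4.1 places dosing "between 3 and 6 days after birth and/or up to 14 days in patients who experience temporary contraindications", and gives the same extension to infants transferred in.

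**Late entry and postponement.** Section 2.3.4 admits infants up to day 14 after transfer or a temporary contraindication, without distinguishing the groups. Section 2.3.6 applies its postponement criteria, up to day 14, to the control matching point as well as to FMT.

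**Role of the markers.** Section 5.1 includes among the events of the primary safety outcome "appearance of symptoms of infection, and increase in inflammation indicators". Section 2.3.3 compares the proportion of infants with at least one AE or SAE between groups.

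**Age-specific limits.** Section 2.3.6 begins its laboratory list with "Elevated inflammation parameters: leukocyte count< 5 and >30 thousand" per µL for the first 48 h. The upper limit is 20 thousand/µL after that, and the procalcitonin threshold is stated only for beyond 72 h. CRP has no age rule.

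**The concern.** A baseline panel shows whether a later abnormality is new. It does this equally in both groups only if it is taken at a similar distance from each infant's time zero. Here one group's limit is a calendar age and the other's is the dose. The two separate as soon as time zero moves away from day 6, which the protocol expressly allows.

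At stake is a component of the primary safety outcome in a comparison of 20 with 20 infants, allocated by alternation and observed open-label. Section 2.3.3 says interpretation will rest on effect estimates and their intervals, so a distortion matters even when no test is significant. There is also a practical defect: some controls whom the eligibility criteria admit cannot satisfy the baseline rule.

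**Working it through.** The plan states no figure for this point, so the check sets the sections side by side.

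**1. Infants on schedule.**
- Control: consent to day 5, matching point day 6. Gap from baseline to time zero: at least 6 − 5 = 1 day, and up to 6 − 0 = 6 days if consent and sampling occur at birth.
- Study: consent to FMT1, with FMT1 on days 3 to 6. Gap: from almost nothing up to 6 days.
- The windows largely overlap. An infant dosed on day 3 must be sampled by day 3, while a control may be sampled on day 5, so the study baselines could be the earlier ones.

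**2. Postponed infants.**
- Control, matching point moved under 2.3.6: the baseline is still capped at day 5. With the matching point on day 12 the gap is at least 12 − 5 = 7 days; on day 14 it is at least 14 − 5 = 9 days.
- Study, FMT1 postponed to the same day: the panel may be drawn that day.
- If 4.4 is read instead as fixing the control time zero at day 6 whatever happens, the control gap stays at 1 to 6 days. That reading contradicts 2.3.6, and postponed study infants would then be followed from a later age than any control.

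**3. Infants transferred in.**
- Control transferred and consented on day 8: eligible under 2.3.4, but a window that closes on day 5 is already past. (This assumes consent is obtained at the trial centre.)
- Study infant in the same position: any panel before FMT1 complies.

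**4. Does baseline age matter on the document's own terms?** For leukocytes, yes: a value of 25 thousand/µL is within the limit at 40 h (30) and above it at 60 h (20). For procalcitonin there is an age condition but no stated direction of change. For CRP there is nothing. Because neither group has an earliest sampling age, baselines before 48 h are possible in both.

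**5. Illustration of sensitivity, not an estimate.** Assumptions, none from the plan: a rise means any follow-up leukocyte value above baseline; levels fall by 30/20 = 1.5-fold after 48 h (a ratio of limits, used here as if it were a ratio of typical levels); log-scale SD s = 0.3 to 0.6; within-infant correlation r = 0.3 to 0.6; one follow-up value; no treatment effect.
- For an infant with an early baseline, P(rise) = Φ(−ln 1.5 / (s√(2(1 − r)))). With s = 0.4 and r = 0.6: Φ(−0.405/0.358) = 0.129.
- For a later baseline, P(rise) = 0.50.
- If a fraction f of one group has early baselines and the other group has none, P(rise) in the first group is f × P(early) + (1 − f) × 0.50. With f = 0.25: 0.25 × 0.129 + 0.75 × 0.50 = 0.407.

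| f in one group, none in the other | P(rise) in that group | P(rise) in the other | Fisher rejection, 20 v 20 |
|---|---|---|---|
| 0 | 0.50 | 0.50 | 2.0% |
| 0.25 | 0.39–0.45 | 0.50 | 3–5% |
| 0.50 | 0.28–0.39 | 0.50 | 5–20% |
| 1.00 | 0.07–0.28 | 0.50 | 19–85% |

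The table applies whichever group has the early baselines. If both have the same share, the difference disappears.

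**The case against.** The strongest reply is that there is no real asymmetry. FMT1 is only a latest permitted time, just as day 5 is for controls, and a study infant may also be sampled on day 1. For infants on schedule this stands.

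The sections also do not say that a rise is measured from point 0. Sections 4.4 and 5.1 list it alongside departures from the norm, and 2.3.6 supplies norms. On that reading two infants with the same value after day 6 are classified alike whatever their baselines. This stands too, and it is why any distortion can only be stated conditionally. Point 0 is still needed on that reading to tell a pre-existing abnormality from a new one.

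Laboratory criteria apply to controls as well: 2.3.6 covers the setting of the matching point and includes follow-up tests. A panel near time zero may therefore exist for a postponed control. Section 4.4 does not make it the baseline.

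A reader might infer that early control baselines hide rises among controls and so make FMT look worse. The documents do not support that. It requires early sampling mainly in controls, a change-from-baseline definition and a fall in level with age, and the protocol establishes none of these. Dosing on day 3 could reverse the imbalance.

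Finally, this is a pilot that disclaims power and admits residual confounding. That limits the consequence but does not reconcile the sections.

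**Conclusion.** The point holds as an internal inconsistency with a conditional statistical consequence. From the wording alone, the day-5 limit in 4.4 does not fit the day-14 allowances in 2.3.4 and 2.3.6. A postponed control can have a baseline 9 days or more before time zero, and a control transferred after day 5 cannot comply, while a comparable study infant can be sampled at dosing. How many infants this affects is not stated.

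Whether the primary comparison is distorted depends on two things the protocol leaves open: whether a rise is judged against point 0, and whether baseline ages actually differ between groups. The document supports age dependence for leukocytes, and an age condition for procalcitonin, but nothing for CRP. It fixes neither the direction nor the size of any bias, and the table above shows sensitivity under assumed values only. A demonstrated bias against FMT would be too strong a conclusion.

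The frequency of follow-up panels also differs between groups. That is a separate matter, which aligning the baselines would not resolve.

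**What to change.** - In 4.2, 4.3 and 4.4, define point 0 for this panel by one window relative to the anchor in both groups: for example, within 24 h before FMT1 in study infants and within 24 h before the infant's actual matching time point in controls, including after postponement or transfer. The exact width matters less than its being the same.
- Remove the fixed day-5 limit from 4.4, and reconcile 4.4 with 2.3.4 and 2.3.6 on when a postponed or late-transferred control has its time zero.
- State that a rise in inflammation markers is judged in both groups against this value, read with the age-specific limits in 2.3.6 where they exist.
- Keep any earlier panel as descriptive data, and report age at baseline by group.

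The cost is protocol wording. The number of planned baseline panels stays at one per infant, and where a control is postponed, the reassessment tests already foreseen in 2.3.6 could serve. The small downside is fewer chances to combine the control draw with an early routine sample.

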## Abstract

**Background/Objectives**: Necrotizing enterocolitis (NEC) is an inflammatory disease with an incidence of about one in 1000 live births, much higher in premature and low birth weight newborns. Intestinal dysbiosis is an important element in the pathogenesis of NEC, and for this reason, experimental models have been used to administer fecal microbiota transplants (FMTs) for prophylaxis and treatment of NEC with very satisfactory results. The primary endpoint of the study is safety, defined as the incidence of adverse events (AEs) and serious adverse events (SAEs) occurring from the time of intervention until hospital discharge, classified according to severity and assessed for relatedness to the intervention. **Methods**: This prospective, single-arm, open-label clinical study will include 20 infants born between 24 0/7 and 36 6/7 weeks of gestation. FMTs will be administered twice as a deep rectal infusion via a Foley catheter. The donors of the material from which the FMT will be prepared will be women in the third trimester of pregnancy. The safety of the therapy will be assessed by comparison with a control group, i.e., 20 patients who will meet the same inclusion criteria and will not meet any of the exclusion criteria, subject to the same hospital observation but without undergoing any medical/therapeutic intervention other than the collection of biological material. **Discussion**: The study will provide data on the safety and initial efficacy of FMT in this group of patients, which will allow for further research into the use of this method in the prevention of infections and NEC. Ethics: The study protocol was approved by the Bioethics Committee of the Medical University of Warsaw, Warsaw, Poland (KB/52/2025). All procedures will follow the principles of the Declaration of Helsinki. The results of the study will be submitted for knowledge translation in peer-reviewed journals and presented at national and international pediatric society conferences. Clinical Trial Registration: The study is registered at ClinicalTrials.gov: ID: NCT06333405.

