#### 2.3.3. Statistical Analysis

All analyses will be conducted on an intention-to-treat basis.

The primary endpoint is safety, defined as the incidence of adverse events (AEs) and serious adverse events (SAEs) during the observation period.

The proportion of patients experiencing at least one AE or SAE will be compared between groups using Fisher’s exact test. The chi-square test will be applied when its assumptions are met.

The incidence of specific AEs will also be compared using Fisher’s exact test. Relative risks (RRs) with two-sided 95% confidence intervals (CIs) will be calculated.

If the number of events per patient is analyzed, between-group comparisons will be performed using Poisson regression or negative binomial regression, depending on data dispersion.

Time to first AE, if applicable, will be analyzed using Kaplan–Meier estimates and compared using the log-rank test.

Continuous variables will be assessed for normality using the ShapiroWilk test. Normally distributed variables will be compared using Student’s *t*-test, and non-normally distributed variables using the Mann–Whitney U test.

Two-sided tests will be used throughout, with statistical significance set at α = 0.05. Estimates will be presented with two-sided 95% confidence intervals. Analyses will be performed using validated statistical software (e.g., R, Stata, or SAS); the exact software and version will be documented in the final report.

Given the limited sample size, the study is not powered for formal hypothesis testing of small effect sizes. Therefore, interpretation will focus primarily on effect size estimates and their 95% confidence intervals rather than solely on statistical significance. Clinically meaningful differences will be considered in the context of effect magnitude and precision.

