#### 2.3.4. Inclusion Criteria

Premature babies born naturally or by caesarean section between 24 0/7 and 36 6/7 weeks of pregnancy.At least 24 h after the end of antibiotic therapy, if it is/was used.Up to 6 days of age OR up to 14 days of age in the case of transfer from another facility or temporary contraindications to the administration of microbiota (defined below).Newborns born in the hospital conducting the experiment and outside of it.Premature infants hospitalized in the intensive care unit and neonatal pathology unit during the study period.Signed informed consent of parents/legal guardians for the child’s participation in the experiment in the study group (with the administration of microbiota)—in the version for newborns born between 24 0/7 and 27 6/7 weeks of pregnancy.B. Signed informed consent of parents/legal guardians for the child’s participation in the experiment in the study group (with microbiota administration)—version for newborns born between 28 0/7 and 36 6/7 weeks of gestation.C. Signed informed consent of parents/legal guardians for the child’s participation in the experiment in the control group (without administration of microbiota)—in the version for the control group.

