## Figures and Tables

**Table 1 pharmaceuticals-19-00437-t001:** Time windows for biological sample collection points.

Sampling Point	Sampling Time	Time Window ***
PRE (point “0”)	First stool after birth *	before administration of the first dose of microbiota (FMT1)
POST7	7 days after FMT2 ** 13th day of life (control group)	±3 days ***
POST14	14 days after FMT2 ** 20th day of life (control group)	±3 days ***
POST30	30 days after FMT2 ** 36th day of life (control group)	±7 days ***
POST60	60 days after FMT2 ** 66th day of life (control group)	±7 days ***
POST120	120 days after FMT2 ** 126th day of life (control group)	±14 days ***

* For preterm infants transported from other hospitals, the PRE stool sample should be obtained from the first stool passed after obtaining parental/guardian consent. ** For the intervention group, counting of “POST” days begins on day 1 after FMT1 administration (matching day). For the control group, counting begins from the infant’s chronological age: POST7 = 6th day + 7 days = 13th day of life, POST14 = 6th day + 14 days = 20th day of life, POST30 = 6th day + 30 days = 36th day of life, POST60 = 6th day + 60 days = 66th day of life, and POST120 = 6th day + 120 days = 126th day of life. *** Samples should be collected within the indicated time windows. If collection is not possible within the window, samples should be collected at the nearest possible time, and deviations must be documented.

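### Adverse-event observation starts on different days of life in the two groups, and the protocol gives two conflicting start rules for controls

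*Protocol article*

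**What the plan says.** - **Endpoint.** The Abstract counts adverse events and serious adverse events "occurring from the time of intervention until hospital discharge". Section 2.3.3 repeats the endpoint but refers only to the observation period. It also states "All analyses will be conducted on an intention-to-treat basis".
- **Study group.** Section 4.1 has FMT given "between 3 and 6 days after birth and/or up to 14 days in patients who experience temporary contraindications", and applies the same upper limit to infants transferred in.
- **Controls, first rule.** Section 4.4: "From day 6 (the matching time point), any adverse events or deviations from the norm will be recorded". Section 4.5 uses the same day to count sampling days, and the Table 1 footnote works it through: "POST7 = 6th day + 7 days = 13th day of life".
- **Controls, second rule.** Section 2.3.6 provides for "postponement of the matching time point for administration of intestinal microbiota doses (control group", on the same temporary criteria as for FMT and up to day 14. A new matching day may be set once the contraindications have cleared.
- **Eligibility.** Section 2.3.4 admits infants "Up to 6 days of age OR up to 14 days of age in the case of transfer from another facility". Section 4.4 wants a control's baseline inflammation bloods taken between consent and the fifth day of life.

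**The concern.** Sections 2.2 and 5.1 make the comparison with controls the basis for judging safety. The main statistic is the proportion of infants with at least one event, and it depends on when counting begins. If one group starts earlier or later than the other, the proportions, relative risks and Kaplan–Meier curves compare different stretches of early life. A difference can then appear, or be hidden, with no effect of FMT.

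The start rule also touches the outcome directly. Signs of infection and raised inflammation markers are reasons to postpone (section 2.3.6), and they are also recordable events (sections 4.4 and 5.1). Whether an infant who is ill on day 6 is counted or postponed therefore changes the endpoint itself.

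**Working it through.** The protocol derives no event rate or sample size, so there is no planned figure to reproduce. The check is of day arithmetic and of the passages against each other.

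**1. Control anchor.** 6 + 7, 14, 30, 60 and 120 gives days 13, 20, 36, 66 and 126. These are exactly the control days in Table 1, which leaves no room for a postponed matching point.

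**2. Offset from a day-6 control** (FMT day minus 6):
- FMT on day 3: 3 − 6 = −3 days
- FMT on day 6: 0 days
- FMT on day 14: 14 − 6 = +8 days

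**3. Overlap of the 72-hour windows.** Section 4.3 follows study infants closely for 72 h after FMT. Section 4.4 ties the control inflammation bloods to the 72 h from day 6, that is days 6 to 9. For FMT on day 3, 4, 5, 6, 8, 10 or 14, the overlap is 0, 1, 2, 3, 1, 0 or 0 days.

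**4. The two control rules side by side.**

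| Situation | Day 6 governs | Postponement governs |
|---|---|---|
| Events on days 3–5 | Can count in study group only | Same: a control never starts before day 6 |
| Control ill on day 6 | Counted, while FMT infants start only after contraindications resolve | Postponed as well, so the groups are treated alike |
| Control transferred in after day 6 | Start precedes enrolment | Same: postponement covers contraindications, not late arrival |

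For a control arriving on day 10, the start lies 10 − 6 = 4 days before arrival, and baseline bloods due by day 5 cannot be taken. The transfer exception in section 4.5 and Table 1 covers only the first stool sample.

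**5. Infants allocated to FMT but never dosed.** If contraindications persist to day 14, the infant stays in the intention-to-treat set. Under the Abstract's wording it has no start of observation.

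**6. Illustration of size.** Hazards and discharge ages here are assumptions. With no treatment effect, P(at least one event) = 1 − exp(−H), where H is the cumulative hazard from the start of counting to discharge.

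| Assumed hazard and discharge | Start day 3 | Start day 6 | Start day 14 |
|---|---|---|---|
| 0.05 per day, discharge day 60 | 0.942 | 0.933 | 0.900 |
| 0.02 per day, discharge day 30 | 0.417 | 0.381 | 0.274 |
| 0.15·exp(−t/7) per day, discharge day 30 | 0.488 | 0.350 | 0.120 |

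For the second row: H = 0.02 × 27 = 0.54, 0.02 × 24 = 0.48 and 0.02 × 16 = 0.32.

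Against a day-6 control, a day-3 start raises the proportion by 0.9, 3.6 or 13.8 points. A day-14 start lowers it by 3.3, 10.7 or 23.0 points. These are extremes in which every study infant starts on that day. A mix of dosing days would partly cancel. With 20 per group one infant is 1/20 = 5 points, so the range runs from less than one infant to between four and five.

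**The case against.** The strongest reply is that day 6 is only a default. Sections 4.4 and 4.5 say it is assumed, section 2.3.6 itself takes day 6 as its reference, and the postponement rule can be read as the exception. On that reading controls are cleared of contraindications too, and the +8-day offset shrinks for contraindicated infants. This stands as a possible reading. A reader might infer that every control is fixed at day 6 and that the illness asymmetry is certain. The documents do not support that, because they state both rules. The default reading still leaves days 3 to 5 and late transfers unresolved, and Table 1 does not carry the postponement through.

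A reader might also infer that undosed infants contribute no events by construction. That rests on the Abstract alone. Section 2.3.3 says only the observation period, section 5.1 covers all adverse events, and the number of undosed infants is unknown. What stands is that the Abstract's wording gives them no start.

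A third temptation is to take the chance of an event during the uncounted days as the share of infants lost. The endpoint runs to discharge, and section 5.3 expects stays of several weeks. An infant with an uncounted early event may well have a later counted one.

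On sampling, the ±3-day windows largely absorb a 3-day offset. They do not absorb 8 days: POST14 is day 14 + 14 = 28 for a day-14 recipient and day 20 for a control on the Table 1 schedule, so the windows are days 25–31 and 17–23.

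Finally, this is a small pilot focused on estimates, and section 5.4 urges caution about causal claims. That tempers interpretation, but it does not mention the observation start and does not correct it.

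**Conclusion.** The point holds in this form: adverse-event observation starts differently in the two groups, and the control start is stated in two incompatible ways. Two consequences follow under either rule: events on days 3 to 5 can count only in the study group, and controls transferred in after day 6 have no workable start. The unequal treatment of infants ill on day 6 follows only if the day-6 text governs. The missing start for undosed infants follows only from the Abstract's wording.

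The start differs by −3 to +8 days. The upper end applies to late-dosed infants set against day-6 controls. The bias in the primary comparison has no derivable size or direction, since the protocol gives no event rates, discharge ages or dosing-day distribution. The range of about 1 to over 20 points rests wholly on the assumed hazards and on extreme dosing days. The matter should be settled before recruitment, because events that were not recorded prospectively cannot be reliably recovered.

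**What to change.** 1. Reconcile section 2.3.6 with sections 4.4 and 4.5 and Table 1, so that one rule for the control matching time point appears throughout.
2. Record adverse events prospectively from enrolment in both groups by the same rule. Run the intention-to-treat primary comparison and the Kaplan–Meier analysis from that start. Late transfers and undosed infants are then covered.
3. Use the matching time point, with its postponement and never earlier than enrolment, only for control POST-day counting and sampling.
4. Report events after FMT1 in dosed infants as a supplementary safety-set summary.

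Giving each control the age at which its neighbour in the sequence received FMT2 would not work. Events between the two doses would count in one group only, and a control admitted before its partner would have no prospective start date.

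The cost is protocol wording and a date field on the case report form. Events before dosing enter the intention-to-treat comparison and dilute it slightly, and control sampling days are no longer fixed calendar ages. The change concerns the observation start only and leaves the timing of FMT as it is.
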